## Abstract

**Background/Objectives:** During radiotherapy for prostate cancer, the risk of radiation cystitis is increased if the volume of the bladder is small. According to previous studies, it is important that bladder volumes are ≥200 mL. Drinking protocols may be helpful in this context. Adherence to such protocols can be challenging, and may be improved by an app reminding patients before each session of radiotherapy to drink a certain amount of water. Our prospective phase 2 trial (REFILL-PAC-HYPO, NCT06784115) evaluates the impact of a reminder app on bladder filling in prostate cancer patients treated with hypo-fractionated radiotherapy. **Methods:** Twenty-seven patients need to be recruited for the REFILL-PAC-HYPO trial. Radiotherapy, preferably with volumetric-modulated arc therapy, uses hypo-fractionation with 20 × 3.0 Gy over four weeks. An app reminds patients to drink water (300 mL) 45 min before each session of hypo-fractionated irradiation. On the last day of their treatment, patients are asked about their satisfaction with the app. In the case of a dissatisfaction rate of >20%, the app requires modifications. If this rate is >40%, the app is considered not useful. Additionally, patients are asked about the impact of their participation in the trial and using the app on their general attitude towards health technology. Furthermore, the phase 2 cohort is compared to a historical control group treated with hypo-fractionated radiotherapy during recent years but not supported by an app. The REFILL-PAC-HYPO trial will contribute to identifying the potential value of a reminder app for bladder filling during hypo-fractionated radiotherapy for prostate cancer.

## 1. Introduction

Many patients with prostate cancer, which is a very common type of cancer, are treated with radiotherapy, either as external beam radiotherapy (EBRT) alone, brachytherapy alone, or a combination of EBRT and brachytherapy [1,2]. Since three randomized trials have demonstrated the non-inferiority of moderately hypo-fractionated EBRT (dose per fraction from >2.0 to 3.4 Gy and overall treatment time from 4 to 5.5 weeks) when compared to normo-fractionated radiotherapy (dose per fraction of 2.0 Gy and overall treatment time from 7.5 to 8 weeks), moderately hypo-fractionated radiotherapy has become more popular, particularly for patients with low or intermediate prostate cancer [3,4,5,6,7]. Two of the three randomized trials used 20 × 3.0 Gy for HF-RT [4,5]. Radiotherapy for prostate cancer, irrespective of the type of fractionation, may lead to significant acute toxicity, including radiation cystitis. It was previously reported that a smaller bladder volume of <200 mL (or <180 mL) led to a higher rate of urinary toxicity [8,9,10]. Furthermore, a planned bladder volume of >200 mL resulted in decreased motion of the prostate during the corresponding radiation sessions [11]. In another study, the recommended dose constraints for the bladder were achieved less frequently if its volume was <200 mL [12]. Thus, it is important that bladder volumes are ≥200 mL during most or even all radiation sessions.

In a recent study, we investigated the bladder volumes in 76 patients receiving moderately hypo-fractionated EBRT alone with 20 × 3.0 Gy, at each of the 20 fractions [13]. The mean and median numbers of radiation fractions with bladder volumes of <200 mL were significantly (*p* < 0.001) higher in the subgroup of patients with bladder volumes of <200 mL prior to the course of moderately hypo-fractionated EBRT. These results indicate a medical need for an improvement in bladder filling status during moderately hypo-fractionated EBRT, especially in patients with bladder volumes of <200 mL prior to the start of the radiation course [13].

Other groups have evaluated the value of drinking protocols where patients were requested to drink water before computed tomography (CT) simulation and each treatment session [10,11,12,14,15,16,17,18,19,20,21,22,23,24]. The amount of water was between 200 and 600 mL and the interval between water intake and CT simulation or daily radiation was between 30 and 60 min [10,11,12,14,15,16,17,18,19,20,21,22,23,24]. Following a drinking protocol may require substantial discipline from patients. Therefore, we decided to create a mobile application (app) that reminds patients before a session of radiotherapy to drink water. The REFILL-PAC-HYPO trial investigates a number of radiation sessions with bladder volumes of <200 mL in a prospective series of patients treated with moderately hypo-fractionated EBRT alone for localized prostate cancer using such a reminder app. In addition, the REFILL-PAC-HYPO trial evaluates whether the use of the reminder app leads to a significant reduction in the proportion of radiotherapy sessions with bladder volumes of <200 mL when compared to a historical control group not supported by a reminder app.

## 2. Experimental Design and Materials

### 2.1. Objectives and Endpoints

The main objective of the REFILL-PAC-HYPO trial is the evaluation of the effect of an app reminding patients receiving moderately hypo-fractionated radiotherapy for localized prostate cancer to drink water before each session of radiotherapy on the number of sessions during which the bladder volume was <200 mL. The app reminds patients to drink 300 mL of water 45 min before each radiotherapy session. The selection of these parameters was based on clinical experience and previous studies [10,11,12,14,15,16,17,18,19,20,21,22,23,24]. When considering these studies, the median time interval between water intake and radiotherapy was 45 min, and, therefore, this was selected for the REFILL-PAC-HYPO trial. Since the median amount of water was 400 mL, this amount was initially chosen for the trial. However, the centers participating noted that a considerable number of patients irradiated for prostate cancer experienced difficulties in retaining urine until the completion of their radiation session if they drank more than 300 mL before the session. Therefore, an amendment of the protocol using 300 mL instead of 400 mL was submitted to and approved by the Ethics Committee. The primary endpoint of the REFILL-PAC-HYPO trial is the number of radiotherapy sessions with a bladder volume of <200 mL at the end of treatment (20 fractions). The secondary endpoints include satisfaction with the app and the impact of participation in the trial and using the app on general attitudes towards health technology. The patients’ adherence to the app is assessed. The patients have to confirm their intake of water each day and receive a puzzle piece as a reward. Moreover, the patients are interviewed by staff members during their daily visits to the radiotherapy department regarding their time and amount of water intake.

### 2.2. General Trial Design and Duration

The REFILL-PAC-HYPO trial is a single-arm multi-center phase 2 study that evaluates the impact of a reminder app on the number of radiotherapy sessions with a bladder volume of < 200 mL during moderately hypo-fractionated radiotherapy for prostate cancer when compared to a historical control group also treated with moderately hypo-fractionated radiotherapy but not supported by an app. This control group is regarded as appropriate, since all patients were irradiated recently (2022–2024) with volumetric-modulated arc therapy (VMAT) at centers participating in the REFILL-PAC-HYPO trial. Moreover, the patients of the control group received Cone Beam Computed Tomography (CBCT) at each session. The time for the recruitment of all 27 patients will be 20 months. As the end of the 4-week course of radiotherapy represents the end of the study, the time for the REFILL-PAC-HYPO trial will be 21 months in total.

### 2.3. Eligibility Criteria

The criteria for inclusion and exclusion are given in Table 1.

### 2.4. Sample Size Calculation

The primary objectives of the REFILL-PAC-HYPO trial are the assessment of the effect of an app reminding prostate cancer patients treated with moderately hypo-fractionated radiotherapy to drink water before each treatment session on the number of sessions with bladder volumes of <200 mL and to demonstrate that this number is lower when compared to a historical control group not supported by a reminder app. To allow for a skewed distribution of the primary endpoint, the Wilcoxon–Mann–Whitney test will be applied for confirmatory statistical analysis. The calculation of the required sample size is based on an article by G.E. Noether [25]. In the external historical control group consisting of 52 patients, the mean number of radiation fractions with bladder volumes of <200 mL was 16.0 (SD 5.5), and the median number was 19.0 fractions (IQR 14.5–20.0) [13]. A decrease in this mean value by roughly 30% (to 11.2 fractions) is considered clinically relevant, based on the findings from our previous study and our clinical experience [13]. For illustrative purposes, translating this decrease into a non-parametric effect size framework (assuming, for simplicity, a normal distribution) leads to a probability of roughly 0.27 that the number of fractions of <200 mL with the reminder app will be larger than without the app. Based on this effect size, a sample size of 24 patients in the prospective REFILL-PAC-HYPO trial is required for the comparison with the historical control group to ensure a 90% power to reach statistical significance with a two-sided Wilcoxon Mann–Whitney-U-test and a 5% significance level. Assuming that roughly 10% of the enrolled patients will not be eligible for the primary analysis, since they may receive less than 20 fractions, a total number of 27 patients should be enrolled in the REFILL-PAC-HYPO trial.

## 3. Detailed Procedure

### 3.1. Assessments

The following characteristics are assessed before the start of the radiotherapy course: medical history, medication, age, body mass index, Karnofsky performance score, bladder volume, prostate volume, tumor stage, histology, Gleason score, level of prostate-specific antigen (PSA), risk group of prostate cancer, dose fractionation parameters, treatment volume, technique of radiotherapy, and patient’s smart phone experience and need for support. The corresponding timeline is given in Table 2.

### 3.2. Treatment and Interventions

#### 3.2.1. Moderately Hypo-Fractionated Radiotherapy

In the REFILL-PAC-HYPO trial, radiotherapy will be administered using moderate hypo-fractionation with 20 × 3.0 Gy over 4 weeks. The preferred technique for the radiation treatment of the prostate plus/minus seminal vesicles is VMAT. Moderately hypo-fractionated radiotherapy for prostate cancer may lead to adverse effects, including cystitis, proctitis, and skin reactions. In the case of grade 3 toxicity according to the Common Terminology Criteria for Adverse Events (CTCAE) version 5.0, radiotherapy may be delayed for up to 7 days without consequences [26]. If the time of delay is longer than 7 days, participation in the trial must be stopped and the principal coordinating investigator must be informed.

#### 3.2.2. Assessment of the Bladder Volume

Bladder volume is assessed by experienced staff members before the radiotherapy course during CT simulation and during each fraction of moderately hypo-fractionated radiotherapy using a CBCT. The staff members contour the urinary bladder, and its volume is calculated by the planning system.

#### 3.2.3. Mobile Application (Reminder App)

In the REFILL-PAC-HYPO trial, the patients are supported by a reminder app, which is developed by Nextlabel OHG from Lübeck. The purpose of the app is to remind the patients to drink 300 mL of water 45 min before each radiotherapy session. The time of the reminder can be set by the patients for each session.

#### 3.2.4. Questionnaire Regarding the App and Its Impact on Using Health Technology

At the end of the course of moderately hypo-fractionated radiotherapy, the patients will complete a questionnaire (modified according to [27,28]) regarding their satisfaction with the reminder app. If more than 20% of the patients are not satisfied, the app needs to be improved and requires modifications. If the dissatisfaction rate is >40%, the app is considered not useful. These thresholds were selected based on the protocols of previous trials by our group developed after discussions with the Ethic Committee responsible concerning this matter [29,30]. In addition, this questionnaire addresses the impact of participation in the trial, including the use of the reminder app, on the patient’s general attitude towards health technology.

### 3.3. Statistical Methods for Primary and Secondary Outcomes

The primary endpoint is defined as the number of radiotherapy sessions with bladder volumes of <200 mL at the end of the course of moderately hypo-fractionated radiotherapy (i.e., after 20 fractions). Descriptive measures of location and dispersion will be used to describe the results of the REFILL-PAC-HYPO trial. The impact of patient characteristics on the primary objective will be assessed using the Wilcoxon two-sample test. These characteristics include age (<75 vs. ≥75 years), Karnofsky performance score (70–80 vs. 90–100), body mass index (<30 vs. ≥30 kg/m^2^), prostate volume (<60 vs. ≥60 mL), pre-radiotherapy PSA level (<10 vs. ≥10 ng/mL), Gleason score (≤7 vs. 8–9), primary tumor stage (T1 vs. T2 or T3 [31]), risk group (low to intermediate vs. high), and antihormonal therapy before and/or during moderately hypo-fractionated radiotherapy (no vs. yes). The cohort of the REFILL-PAC-HYPO trial will be compared with the corresponding historical control group by a two-sided Wilcoxon–Mann–Whitney two sample test (significance level = 5%). A high degree of comparability between the prospective and retrospective patient data sets is expected. The potential heterogeneity of study populations is identified by comparing the above-mentioned characteristics using Wilcoxon–Mann–Whitney tests. Homogeneity is assumed if *p*-values are >0.20. Any factor indicating a tendency towards heterogeneity (*p* < 0.20) will be included in a multivariate count data Poisson regression model, including the number of radiotherapy sessions with bladder volumes of <200 mL as dependent variable. Corresponding characteristics and the binary factor (prospective cohort vs historical control group) are considered as independent variables. In the case of overdispersion, the Poisson model is replaced by a negative binomial model. In addition, a propensity score matching approach considering the above-mentioned patient characteristics will be applied to reduce the risk of selection bias.

Since no comparison with the historical control group is possible regarding the secondary objectives, these analyses focus only on descriptive analyses. The patient satisfaction results will be used to decide whether the reminder app needs modification. If the dissatisfaction rate is >20%, the app needs modifications. If the dissatisfaction rate is >40%, the app is considered not useful for improving the bladder filling status of patients treated with moderately hypo-fractionated radiotherapy for localized prostate cancer.

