Our previous study identified significant differences between patients with a pre-radiotherapy bladder volume of <200 mL and those with a volume of ≥200 mL regarding the number of fractions with a volume of <200 mL during a radiotherapy course of 20 fractions [13]. The mean and median numbers of fractions with a volume of <200 mL were 16.0 vs. 7.9 and 19.0 vs. 8.0, respectively. As a consequence, the REFILL-PAC-HYPO trial is limited to patients with a pre-radiotherapy bladder volume of <200 mL, since these patients are much more likely to benefit from the reminder app. For the comparison of the REFILL-PAC-HYPO cohort to the historical control group, a matching procedure is performed that considers nine patient- and tumor-related factors.

However, this study has several limitations that need to be considered when interpreting its results when they become available. Its single-arm design cannot exclude the Hawthorne effect, the small sample size may result in an insufficient statistical validity, and the historical control group may have unmeasured confounders due to retrospective data. The fact that patients in the REFILL-PAC-HYPO cohort must own a smartphone and be capable of using the app bears the risk of a selection bias. The urinary bladder is contoured by experienced staff members, and the bladder volume is automatically calculated by the planning system. However, the risk of an observer bias remains, since investigators know which patients use the reminder app. Blinding is not possible, since all patients participating in the prospective trial are supported by the app. In general, this lack of randomization could impact the trial’s internal validity.

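### Bladder volume at CT simulation, the only predictor with a reported effect on the endpoint, is left out of the comparability check, the count regression and the propensity score

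*Protocol article*

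**What the plan says.** All references are to the protocol article.

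- **The list (Section 3.3).** It opens "These characteristics include age (<75 vs. ≥75 years), Karnofsky performance score (70–80 vs. 90–100", adds body mass index, continues "prostate volume (<60 vs. ≥60 mL), pre-radiotherapy PSA level (<10 vs. ≥10 ng/mL), Gleason score (≤7 vs. 8–9" and ends with T stage, risk group and antihormonal therapy. That makes nine. The Discussion (Section 4) also counts nine factors in the matching, so the list is not an open set of examples.
- **Its three uses (Section 3.3).** For comparability: "The potential heterogeneity of study populations is identified by comparing the above-mentioned characteristics using Wilcoxon–Mann–Whitney tests". For the Poisson or negative binomial model, the entry rule is "Any factor indicating a tendency towards heterogeneity", defined as p < 0.20. For matching: "a propensity score matching approach considering the above-mentioned patient characteristics will be applied to reduce the risk of selection bias".
- **Baseline measurement (Section 3.1).** The items recorded before treatment include "body mass index, Karnofsky performance score, bladder volume, prostate volume, tumor stage". Section 3.2.2 says that bladder volume is contoured at CT simulation.
- **Reported effect (Section 4).** For pre-treatment volume below versus at or above 200 mL: "The mean and median numbers of fractions with a volume of <200 mL were 16.0 vs. 7.9 and 19.0 vs. 8.0, respectively". The Introduction gives p < 0.001 for this difference.
- **Restriction.** Table 1 requires a simulation volume below 200 mL. The 52 controls in Section 2.4 have mean 16.0 and median 19.0, the figures that Section 4 gives for the subgroup below 200 mL.

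**The concern.** Simulation volume is the baseline value of the quantity that defines the endpoint, judged against the same 200 mL line. In Section 3.1 it stands between Karnofsky score and prostate volume. Both of those neighbours are in the analysis list and it is not.

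Eligibility sets an upper limit on the variable but does not equalise it. A patient at 60 mL and one at 190 mL both qualify, and it is plausible that they differ in how often they stay below 200 mL. The controls' SD of 5.5 and IQR of 14.5–20.0 show that outcomes still vary within the stratum.

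The comparison is not randomised, and Section 4 itself concedes possible selection through smartphone ownership. If the app cohort started with fuller bladders than the controls, fewer sessions below 200 mL would be expected without any app effect. None of the tests or adjustments named in Section 3.3 would bring that difference to light or correct for it.

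**Working it through.** **1. The design figure.** Inputs from Section 2.4: control mean 16.0, SD 5.5, target 11.2, 52 controls, 90% power, two-sided 5%.

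- Target difference: 16.0 − 11.2 = 4.8 sessions, or 4.8/5.5 = 0.87 SD.
- Effect size: p = Φ(−0.87/√2) = 0.2686 (stated: roughly 0.27).
- Noether's formula: N = (1.960 + 1.282)² / [12·c(1−c)·(p − 0.5)²]. With c = 24/76, N = 75.7, which is within 24 + 52 = 76.
- Enrolment: 24/0.9 = 26.7, so 27.

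The plan's 24 and 27 are reproduced. Neither depends on the covariate list.

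**2. The reported effect of simulation volume.** 16.0 − 7.9 = 8.1 sessions, or 8.1/5.5 = 1.47 control SDs. This contrast lies across the 200 mL cut and both groups are below it, so it cannot itself arise between them. The article gives no effect within the range below 200 mL.

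**3. What a residual imbalance might be worth.** Assume that the two strata differed in mean simulation volume by 100 to 200 mL, and that the slope carries over linearly below 200 mL. Neither assumption comes from the article.

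| Assumed stratum gap | Sessions for a 20 mL imbalance | Share of 4.8 |
|---|---|---|
| 100 mL | 8.1/100 × 20 = 1.62 | 34% |
| 150 mL | 8.1/150 × 20 = 1.08 | 23% |
| 200 mL | 8.1/200 × 20 = 0.81 | 17% |

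**4. What that would do to the unadjusted test.** With no app effect, 24 vs 52 patients and a prognostic difference of b sessions, θ = Φ(−(b/5.5)/√2). The chance of a significant result favouring the app is Φ(√(12·c(1−c)·76)·|θ − 0.5| − 1.96), where the square root is 14.04.

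| b (sessions) | θ | Chance of a false result for the app |
|---|---|---|
| 0.5 | 0.474 | 5.5% |
| 1.0 | 0.449 | 11% |
| 1.5 | 0.424 | 19% |
| 2.0 | 0.399 | 30% |

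The nominal value is 2.5%. This uses the same normal simplification as Section 2.4.

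**5. A check that does not assume linearity.** A lognormal model of simulation and session volumes was fitted roughly to the reported means. It gave 15.9 and 8.1 sessions in the two strata, with SD 5.0 in the lower one. Within the range below 200 mL, the mean count fell from 18.6 (under 100 mL) to 12.2 (175–200 mL). An app cohort with a mean 18 mL higher had 1.0 fewer sessions and false results for the app in 14% of simulated trials. At 31 mL higher the figures were 1.9 sessions and 36%. The volume distribution is assumed, so these are illustrations and not estimates from this trial.

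**6. Why the p < 0.20 entry rule is not enough.** Assume an SD of 40 mL for simulation volume. The standard error of the group difference is 40·√(1/24 + 1/52) = 9.9 mL. A true 20 mL difference is 20/9.9 = 2.03 standard errors and passes p < 0.20 with probability about Φ(2.03 − 1.28) = 77%. It would be missed about 23% of the time.

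**The case against.** Much of the case on the other side stands.

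- **Restriction controls the one contrast that has been shown.** A reader might infer that the 8.1-session gap could appear between the groups. It cannot, because both lie below 200 mL. Only unquantified variation in that range remains.
- **It is not shown to be the strongest predictor.** A reader might infer this from 16.0 vs 7.9. The article reports no effect for any of the nine listed factors, so no ranking is possible. It is the only predictor with a reported effect.
- **The magnitudes are assumed.** Controls sit near the ceiling of 20 (median 19.0), so a linear slope is doubtful. Chance imbalance is already covered by the 5% level. With an SD of 40 mL, 20 mL is about two standard errors and would need a systematic cause. The controls were treated in 2022–2024 at participating centres, which makes a large shift less likely. The conceded smartphone selection leaves one possible.
- **The false-positive rates belong to the unadjusted Wilcoxon–Mann–Whitney test.** Adding a covariate to the regression and the matching leaves that test's error as it is.
- **A baseline table might show the imbalance.** The full protocol and analysis plan are not at hand, and tabulating a recorded baseline item is routine. It would be too strong to say that nothing could reveal a difference. What holds is that no named test or adjustment uses simulation volume.

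These points limit the size of the finding and leave the omission in place. The article closes the list at nine, and the three steps built on it are its planned statistical safeguards against confounding.

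**Conclusion.** The point holds as a gap in the supporting analyses. The article measures simulation volume, reports its effect on the endpoint and uses it to define the population, then leaves it out of every comparability and adjustment step in Section 3.3. Variation below 200 mL is therefore uncontrolled in a non-randomised comparison.

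That omission is certain from the text, but the size of its consequence is not. The 0.8–1.6 sessions for a 20 mL imbalance (17–34% of the target) rest on an assumed 100–200 mL gap between strata and on linearity. The article does not show that such an imbalance exists. Nor does it support reading the omission as a fault in the confirmatory test's specification or in the sample size. The change is well worth making, but the plan does not fail without it.

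**What to change.** In Section 3.3:

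1. Add bladder volume at CT simulation to the list, as a continuous variable in mL.
2. Compare and report its distribution in the app cohort and the controls.
3. Include it in the Poisson or negative binomial model and in the propensity score whatever its baseline p-value.
4. Make the matching statement in Section 4 agree: ten factors instead of nine.

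The confirmatory test remains unadjusted and the sample size remains 24 evaluable and 27 enrolled. The gain is that the comparability check can reveal a difference in starting volume, and the adjusted and matched analyses can show whether the result survives it.

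The cost is small. One more covariate in a match of about 24 app patients to 52 controls may lose some pairs. The controls' values in mL must also be retrieved. That they exist is inferred from the controls' classification as below 200 mL, since the article does not say so. The change should be made before outcomes are analysed.

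### The covariate-adjusted comparison uses Poisson or negative binomial regression for a count capped at 20 and crowded at that cap; a bounded model would be better calibrated and modestly more powerful

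*Protocol article*

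**What the plan says.** The primary endpoint is the number of sessions with a bladder volume below 200 mL "at the end of the course of moderately hypo-fractionated radiotherapy (i.e., after 20 fractions"), so it can take only the values 0 to 20 (protocol article, section 3.3).

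The confirmatory comparison is a two-sided Wilcoxon–Mann–Whitney test at 5%, which section 2.4 chooses because the endpoint may be skewed.

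For confounding, section 3.3 screens nine patient characteristics. Any with p < 0.20 between the cohorts is "included in a multivariate count data Poisson regression model, including the number of radiotherapy sessions with bladder volumes of <200 mL as dependent variable". It adds: "In the case of overdispersion, the Poisson model is replaced by a negative binomial model". Propensity score matching is planned as well.

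Section 2.4 describes the controls (52 patients): the mean number of sessions below 200 mL "was 16.0 (SD 5.5), and the median number was 19.0 fractions (IQR 14.5–20.0"). The target is a mean of 11.2, about 30% lower.

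**The concern.** Poisson and negative binomial models have no upper limit, and their variance grows with the mean. A count out of 20 behaves differently: its spread is squeezed as the mean approaches 20. The control upper quartile equals the maximum, so at least about a quarter of controls sit at the ceiling. The plan allows for skewness in the unadjusted test but not in the adjusted model.

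The adjusted model matters because the trial is single-arm with a historical control, and the Wilcoxon test adjusts for nothing. The regression is one of two planned safeguards against measured confounding. It will probably be run: if the nine screened factors were independent and truly balanced (an assumption), at least one would still fall below 0.20 with probability 1 − 0.8⁹ = 0.87. At stake is whether a real app effect looks weaker after adjustment than it should.

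**Working it through.** **Inputs.** From section 2.4: 52 controls, mean 16.0, SD 5.5, median 19.0, IQR 14.5–20.0; app target 11.2; effect size 0.27; 24 evaluable and 27 enrolled; 90% power, two-sided 5%. From section 3.3: the maximum of 20 and the two regression models. Assumed, because the documents do not give them: a beta-binomial shape and the app-group SD (range 5.5 to 6.8).

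**1. The plan's own figure.** Φ(−4.8/(5.5 × √2)) = 0.2686, the stated 0.27. Noether's formula with 24 and 52 patients (c = 24/76) gives power Φ(√(12 × c(1−c) × 76) × |0.2686 − 0.5| − 1.96) = 0.901. Then 24/0.9 = 26.7, so 27. The sample size is reproduced. The 0.27 comes from an SD of 5.5 in both groups.

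**2. Which model would be used.** Control variance is 5.5² = 30.25, and 30.25/16.0 = 1.9. At mean 11.2 with the same SD the ratio is 30.25/11.2 = 2.7. Poisson requires 1. In simulation, overdispersion was flagged in 93–99% of runs.

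**3. Distributional fit.** Poisson with mean 16 puts 13% of patients above 20. A negative binomial matched to SD 5.5 has k = 16²/(30.25 − 16) = 17.96 and puts 20% there. These values are impossible.

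**4. Variance pattern.**
- Negative binomial at mean 11.2: 11.2 + 11.2²/17.96 = 18.2, SD 4.3.
- Sample-size assumption: SD 5.5.
- Bounded count with the controls' within-patient correlation: ρ = (30.25/(20 × 0.8 × 0.2) − 1)/19 = 0.445; variance 20 × 0.56 × 0.44 × (1 + 19 × 0.445) = 46.6, SD 6.8.

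The negative binomial expects a smaller spread in the app group than either alternative.

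**5. Simulation.** 24 app and 52 control patients, 4,000 runs per row, no covariates. The assumed control distribution has median 19, quartiles 14 and 20, and 43% of patients at exactly 20, close to the published summary. Monte Carlo error is at most 0.8 points. Quasi-binomial uses a t reference.

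| App mean, SD | NB rejects | NB coverage | Quasi-binomial rejects | Gap (points) |
|---|---|---|---|---|
| 16.0, 5.5 (no effect) | 3.0% | 97.0% | 4.7% | – |
| 11.2, 5.5 | 88.3% | 94.9% | 90.9% | 2.6 |
| 11.2, 6.5 | 83.3% | 94.0% | 88.2% | 4.9 |
| 11.2, 6.8 | 79.3% | 93.8% | 86.4% | 7.1 |
| 12.8, 5.5 | 56.2% | 95.4% | 61.2% | 5.0 |
| 12.8, 6.6 | 46.2% | 95.0% | 55.4% | 9.2 |

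- With three binary covariates (1,000 runs, app SD 5.5), the negative binomial rejected 2.9%, 84.5% and 53.3% at app means 16, 11.2 and 12.8. Quasi-binomial rejected 4.2%, 88.0% and 58.5%.
- In the same runs beta-binomial regression rejected 5.6%, 97.9% and 82.7%. Its power is an upper bound, because that model also generated the data.
- When only 33–40% of app patients respond, with large reductions, negative binomial coverage at mean 11.2 was about 92%.
- Plain Poisson rejected 15.3% under no effect and covered 78.4% at mean 11.2, SD 5.5.
- Logistic regression with uncorrected robust standard errors rejected about 6% under no effect.

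**The case against.** The strongest reply is that the regression is not the confirmatory analysis. The Wilcoxon–Mann–Whitney test is, and neither it nor the 24/27 patients depends on the regression. Matching gives a second route to adjustment. This stands, and it sets the severity.

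Second, a reader might infer a power loss of 6–10 points by comparing the planned model with robust logistic regression. That comparison is not like for like, because the robust model rejects about 6% under no effect and the negative binomial about 3%. With both calibrated to 5%, the two are almost equal (85.8% against 85.7% at mean 11.2, SD 6.85). This also stands: most of the gap is a difference in test size. The comparison with quasi-binomial regression is fairer, since that model holds its size. The trial would also apply the nominal cut-off, so it would bear the cost of the conservatism.

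Third, a reader might infer that the planned intervals are simply wrong. At mean 11.2 with SD 5.5 the negative binomial covers about 95%. Coverage near 92% needs uneven response patterns that the protocol does not describe.

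Fourth, probability above 20 shows poor fit and is not in itself an inferential error. The log-link coefficient still estimates a ratio of means, which matches the 30% target directly.

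**Conclusion.** The point holds for the supporting adjusted analysis only. The plan fixes an unbounded model for a count out of 20 whose control distribution sits at the ceiling. The model almost certain to be used, the negative binomial, is conservative when both groups are near that ceiling (about 3% rejection, 97% coverage). It covers about 92–95% at the planned effect and loses roughly 3–9 points of power against a correctly sized quasi-binomial model. The roughly 15% type I error applies only if Poisson were kept despite the overdispersion rule.

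The documents do not support the stronger reading that the trial's main conclusion is at risk or that the model would manufacture a benefit: the negative binomial errs towards caution under no effect. The sizes rest on an assumed beta-binomial shape and app-group SD, because the ceiling is documented for the controls only. This is a worthwhile improvement, not a must-fix.

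**What to change.** In section 3.3, replace the Poisson/negative binomial sentences with: quasi-binomial logistic regression for sessions below 200 mL out of 20, tested against a t reference, or beta-binomial regression. The denominator can be a constant 20, since section 2.4 treats patients with fewer than 20 fractions as not eligible for the primary analysis and a cone-beam CT is taken at each session. If robust standard errors are preferred, add a small-sample correction. Report the model-based difference or ratio in mean sessions below 200 mL alongside the odds ratio, so that the result maps to the 30% target.

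Cost: one or two sentences, settled before outcomes are analysed, with no new data or patients. The small downside is that an odds ratio is less directly interpretable than a rate ratio; reporting the means offsets this.
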